**3. Provide a justification for the sample size used in this protocol.**

*No prior work has studied adipose immune cell health in bariatric patients before or after surgery or in response to Ex+CR.* As a result, data collected in the proposed study will serve as preliminary work to determine power analysis for future studies and NIH proposed grants.

Nonetheless, the appropriate sample size required for significant differences following Ex+CR testing and surgery was, however, determined from our preliminary work (6, 11) on insulin resistance given it’s direct relation to adiposity-related immunity. A delta of 2 (Pre = 3.5 vs. Post = 5.5 surgery), SD of 1.2 with 80% power and an alpha of 0.05 indicates that **5** subjects are needed to show insulin resistance differences post-surgery, which is consistent with Ex+CR reducing insulin resistance in **6** people (Pre = 2.5 vs. Post = 4.9), SD of 1.5 at 80% power. **Thus, assuming a 20% dropout rate, 8 are required per group** **undergoing bariatric surgery.**

In contrast, subjects undergoing diet+exercise vs. diet intervention will require more subjects. This is based on an diet+exercise published study (43) on insulin resistance and energy deficit (i.e. weight loss). A delta of 3.1kg (Exercise = 3.7kg vs. Exercise+diet = 6.8kg), SD of 3.1kg with 80% power and an alpha of 0.05 indicates that **10** subjects are needed to show energy deficit differences. **Thus, assuming a 20% dropout rate, 14 will be required per group** **NOT undergoing bariatric surgery.**

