
# Hypothesis to be Tested

The central hypothesis is that pre-operative metabolic health is an important predictor of bariatric surgery effectiveness. We hypothesize that there is an adipose-derived immunosignature that predicts post-operative recurrence of obesity related CVD abnormalities and that targeting reductions in obesity BEFORE surgery will enhance the success of bariatric surgery on this disease risk. We expect that the combination of exercise and diet will be more successful at improving insulin sensitivity and reducing immune cell dysfunction compared to diet alone as well as expect that exercise will be superior to standard of care alone. These separate studies are expected to provide unique insight to the mechanism by which diet and/or exercise impact immune metabolism in obese patients, and this will shape the development of future studies in bariatric patients per se.

Primary Objectives:

1. **Ascertain the effects of Ex+CR vs. CR in obese subjects and Ex vs. standard of care (SC, i.e. control) BEFORE surgery on cardiometabolic risk.**
2. **Examine the effects of Ex+CR vs. CR in obese subjects and Ex vs. standard of care (SC, i.e. control) BEFORE surgery on surgical complications and quality of life.**
3. **Determine if circulating immunophenotyping after Ex+CR vs. Ex vs. CR vs. SC correlate with immune composition of adipose cell depots (omental and subcutaneous) at the time of surgery or post-intervention testing**.

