**►IF YES, explain the kind of controls to be used.**

Subjects will have pre-intervention testing to determine efficacy of exercise and/or diet on insulin sensitivity and immune health.

1. **What is the study design?**

Matched pair, prospective design. Bariatric patients will be match paired to the exercise or standard medical care group. Subjects not undergoing bariatric surgery will be randomized to calorie restriction or calorie restriction + exercise groups.

1. **Does the study involve a placebo?**

No

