**2. Describe expected rate of screen failure/ dropouts/withdrawals from all sites.**

Based on prior work by our group, we anticipate that 20% of subjects who receive randomization (i.e. treatment) in the study will withdraw/drop out early.

For individuals not receiving bariatric surgery, we anticipate that 30% of subjects who are initially recruited to participate in the screening visits will not meet the criteria for inclusion in the study (i.e. not passing physical examination, abnormal ECG, abnormal exercise test, abnormal blood chemistries, outside of BMI range, pregnancy). Therefore, we expect to screen 38 individuals not receiving bariatric surgery for participation in the study. Of the 38 subjects screened, 28 will undergo the treatment. Accounting for dropouts, 24 subjects will complete the study.

For individuals receiving bariatric surgery, we anticipate 20% of subjects who are initially recruited to participate in the screening visits will not meet the criteria for inclusion in the study (i.e. not passing physical examination, abnormal ECG, abnormal exercise test, abnormal blood chemistries, outside of BMI range, orthostatic intolerance). Therefore, we expect to screen 20 individuals receiving bariatric surgery for participation in the study. Of the 20 subjects screened, 16 will undergo the treatment. Accounting for dropouts, 12 subjects will complete the study.

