***Phase 4: Interventions***

Prior to the intervention subject’s undergoing bariatric surgery will be match paired to receive either standard medical care (SC) or exercise + standard care for 4 weeks. Subject’s not undergoing bariatric surgery will then be randomized to the exercise + diet + standard care group or diet + standard care group for 2 weeks.

*Standard medical care:* If subjects are assigned to this group they will not be provided materials to consume healthy diet and increase exercise participation. Subjects will also be asked to participate in the standard education sessions that are provided to all bariatric surgery patients. This standard care includes meetings with a nutritionist, a psychologist, and a bariatric surgeon.

*Diet + standard medical care*: If subject’s are assigned to this group they will be instructed to follow a weight loss diet plan, created for them by the research team. The diet will restrict your caloric intake to 1000-1400 calories per day. Subject’s will be given two meal replacement shakes each day and advice for preparing a standard, calorie-limited dinner designed for weight loss. Subjects are required to pick up food at least 1 time a week. Subjects will return empty bottles of meal shakes to confirm compliance.

*Exercise training* + *standard medical care for bariatric patients*: If subject’s are assigned to this group they will participate in exercise training and the standard medical care outlined above. Subject’s will be asked to exercise 5 days/week. Subject’s will be able to attend regularly supervised and scheduled training sessions with the exercise physiology staff members in Memorial Gym or they can exercise on their own. Overall, the training program will ask subject’s to exercise 5 times per week and 30 min/day. Subject’s heart rate will be monitored continuously during all training sessions, and they will be asked to exercise at an intensity 65-85% of their previously measured HRmax. Walking will be the main type of exercise. In addition to this training program, subject’s will participate in the standard education sessions that are provided to all bariatric surgery patients.

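### The 8 per bariatric group is justified by pre-to-post changes, so its stated 80% power does not apply to the primary exercise versus standard care comparison

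*Protocol*

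**What the plan says.** Protocol, Statistical Considerations, item 3 (sample-size justification) gives two calculations for the bariatric groups. The first is for the change after surgery: "A delta of 2 (Pre = 3.5 vs. Post = 5.5 surgery), SD of 1.2 with 80% power and an alpha of 0.05", for which it states 5 subjects. The second is for exercise plus caloric restriction (Ex+CR): "Pre = 2.5 vs. Post = 4.9), SD of 1.5 at 80% power", for which it states 6. It then concludes: "Thus, assuming a 20% dropout rate, 8 are required per group".

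The bariatric arms are defined under Study Design: "Bariatric patients will be match paired to the exercise or standard medical care group". Phase 4: Interventions describes them as "standard medical care (SC) or exercise + standard care for 4 weeks". All of these patients then have surgery.

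The first primary objective, under Hypothesis to be Tested, asks for the effect of "Ex vs. standard of care (SC, i.e. control) BEFORE surgery on cardiometabolic risk". Statistical Considerations, item 2 compares the primary outcomes between groups or conditions. Item 4 tests group by time with a repeated-measures ANOVA and adds paired t-tests for within-treatment effects.

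Human Participants, item 2 gives the expected bariatric numbers: "Of the 20 subjects screened, 16 will undergo the treatment. Accounting for dropouts, 12 subjects will complete the study".

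**The concern.** The calculation and the objective concern different quantities. A pre-to-post change in one group shows whether patients change. The primary objective asks whether exercise patients change more than standard-care patients before surgery.

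Neither assumed effect can stand in for that contrast. Both bariatric arms have surgery, and the primary comparison comes before it. Ex+CR is given to neither bariatric arm. The section assumes no Ex-minus-SC difference at all, yet presents 8 per group as the number required.

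What is at stake is the reading of a null result. If Ex and SC do not differ significantly, a reader who takes the 80% at face value may treat that as adequately powered evidence of no effect.

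**Working it through.** **Inputs.** Surgery change 2.0 with SD 1.2; Ex+CR change 2.4 with SD 1.5; alpha 0.05; power 80%; dropout 20%; 8 per group (all Statistical Considerations, item 3). Expected bariatric completers: 12 in two groups, so 12 / 2 = 6 per group (Human Participants, item 2). Two assumptions are mine: tests are two-sided, since the protocol does not say, and the quoted SDs are SDs of within-subject change.

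**Step 1: reproduce the protocol's figures.** Paired t-test, noncentrality = (delta/SD) × √n, n − 1 degrees of freedom.

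- Surgery: 2.0/1.2 = 1.667. At n = 5 the noncentrality is 1.667 × √5 = 3.73 and power is 79.3%; at n = 6 power is 89.9%. Stated: 5.
- Ex+CR: 2.4/1.5 = 1.60. At n = 5 power is 76.2%; at n = 6 it is 87.5%. Stated: 6.
- Dropout: 6/0.8 = 7.5, rounded up to 8. Stated: 8.
- The same method gives exactly the 10 stated for the non-bariatric comparison (delta 3.1, SD 3.1; power 80.3% at n = 10).

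Two-sided two-sample t-tests with the same inputs would need 7 and 8 completers per arm. The paired t-test is the best fit, though not the only near one: one-sided two-group variants give 5 and 5, or 6 and 6.

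**Step 2: power for Ex versus SC.** With two time points, the group-by-time test for two groups is a two-sample t-test on change. Noncentrality = (difference/SD) × √(n/2), with 2n − 2 degrees of freedom. The difference giving 80% power is:

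| Completers per group | In SD | Units at SD 1.2 | Units at SD 1.5 |
| --- | --- | --- | --- |
| 6 | 1.80 | 2.15 | 2.69 |
| 7 | 1.63 | 1.96 | 2.45 |
| 8 | 1.51 | 1.81 | 2.26 |

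The protocol gives no Ex-minus-SC difference, so I show a range of assumed values at SD 1.2:

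| Assumed difference | Power, 6 per group | Power, 8 per group |
| --- | --- | --- |
| 2.0 (whole surgery change) | 74% | 87% |
| 1.5 | 50% | 64% |
| 1.0 (half of it) | 26% | 34% |
| 0.5 | 10% | 12% |

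**Step 3: precision.** 95% CI half-width = t × √(2/n) × SD. At n = 6: 2.228 × √(2/6) = 1.29 SD, i.e. 1.29 × 1.2 = 1.5 units or 1.29 × 1.5 = 1.9 units. At n = 8: 2.145 × √(2/8) = 1.07 SD.

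**Step 4: sensitivity to the SD reading.** If 1.2 were a cross-sectional SD, the SD of change would be 1.2 × √(2(1 − r)) for pre/post correlation r. With 6 per group the detectable difference would then be 3.05, 2.15, 1.67 or 0.96 units for r = 0, 0.5, 0.7 or 0.9 (assumed range).

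**The case against.** **The study calls itself preliminary.** The sample-size section opens by saying that the data will inform power calculations for later work. That softens the consequence. But the same section goes on to give a sample size for significant differences at 80% power, and Human Participants, item 1 ties the total to statistically significant results. The power claim is therefore made.

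**The protocol never says in so many words that Ex versus SC has 80% power.** The figure of 5 is openly a pre/post statement, and item 4 plans paired t-tests within treatment. This stands: the 5 and 6 match an analysis that is planned, so they should be relabelled rather than deleted. It does not help the primary objective, for which no other basis is given.

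**A stronger reading is tempting.** A reader might infer that only a difference larger than the whole assumed surgery effect could be detected. The documents do not support this as a general statement.

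- It holds narrowly at 6 completers (2.15 against 2.0) and fails at 7 (1.96) and 8 (1.81).
- The 6 comes from a loss of 4 in 16, or 25%, whereas the stated 20% would leave 16 × 0.8 = 12.8.
- If all 36 expected completers (24 + 12) shared one error term with 32 degrees of freedom and a common SD, the figure at 6 per group would be 2.00, a tie. A Bonferroni correction for two comparisons would raise it to 2.22.
- The 2.69 at SD 1.5 belongs beside the Ex+CR change of 2.4, not the surgery change of 2.0.

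**The BMI matching might add precision.** Analysed as 6 pairs at SD 1.2, the detectable difference is 2.44 with no within-pair correlation, and it falls below 2.0 only above a correlation of about 0.33. Item 4 does not use the pairing for group differences.

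**Conclusion.** The concern holds as a mismatch between objective and justification. The protocol's arithmetic essentially reproduces; it answers a different question. The stated 80% belongs to within-group pre/post tests and does not carry over to Ex versus SC before surgery.

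For that comparison the planned number gives 80% power only for differences of about 1.5 SD (all 8 per group complete) to 1.8 SD (6 complete). At the expected 6, half the surgery change has about 26% power.

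These sizes rest on a two-sided two-sample t-test on change and on the quoted SDs being SDs of change, which the paired reproduction requires. The mismatch itself depends on neither assumption.

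**What to change.** In Statistical Considerations, item 3:

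1. Label the 5 and 6 as supporting only the within-group pre/post tests.
2. State that, for Ex versus SC, 8 enrolled per group gives 80% power only for differences of about 1.5 to 1.8 SD (8 down to 6 completers per group), and name the SD assumption.
3. Describe Ex versus SC as a preliminary estimate, reported as a mean difference with its 95% CI and an expected half-width of about 1.3 SD at 6 completers per group. Add that a non-significant result is not evidence of no effect.

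The cost is a protocol wording change. Enrolment, procedures and planned analyses stay as they are. The power claim becomes weaker but correct.

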**2. What are the statistical considerations for the protocol?**

This study is a between-within subjects repeated measures design in which insulin sensitivity will be measured before and after interventions across 4 experimental conditions. The outcome measures to be assessed are as follows:

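### The non-bariatric sample size uses a paired formula for two randomised groups, so planned completers give about 61–65% power for 1 SD, and its assumed effect belongs to another contrast

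*Protocol*

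**What the plan says.** Statistical Considerations, item 3, gives a separate calculation for the subjects who do not have bariatric surgery. It is introduced as sizing diet+exercise against diet and takes its inputs from a published study: "A delta of 3.1kg (Exercise = 3.7kg vs. Exercise+diet = 6.8kg), SD of 3.1kg with 80% power and an alpha of 0.05 indicates that". The requirement it arrives at is 10, to detect a difference in energy deficit. A 20% dropout allowance then takes this to 14 per group.

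The comparison itself is fixed elsewhere in the protocol:

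- Primary Objective 1 (Hypothesis to be Tested): "Ascertain the effects of Ex+CR vs. CR in obese subjects and Ex vs. standard of care". The non-bariatric contrast is therefore Ex+CR versus CR.
- The study design item, Phase 4 (Interventions) and the note under the non-bariatric visit schedule all say that non-bariatric subjects are randomised to one of these two arms. Phase 4 gives the diet to both.
- Statistical Considerations, item 4, plans a group-by-test repeated measures ANOVA and keeps paired t-tests for changes within a treatment.
- Human Participants, item 2, forecasts the non-bariatric numbers: "Of the 38 subjects screened, 28 will undergo the treatment. Accounting for dropouts, 24 subjects will complete the study". That is 14 treated and 12 completing per group.

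**The concern.** Two independent groups, a difference of one SD and 80% power cannot be met with 10 per group. The figure is what a single-sample or paired calculation returns. The calculations just before it in the same item compare values before and after treatment, where a paired formula is in place, and it appears to have been carried over to a comparison between groups.

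The size of the effect is a second problem. Exercise versus exercise plus diet holds exercise constant and varies diet. In this trial both non-bariatric arms receive the diet and only exercise differs. Correcting the formula would therefore still leave the calculation resting on an effect that the trial does not estimate.

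At stake is the power claimed for half of Objective 1. A reader of the protocol would expect a 20% chance of missing a true 1-SD difference. With the planned completers, two-sided, that chance is about 35% to 39%.

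**Working it through.** **Inputs** (Statistical Considerations, item 3, unless noted)

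- Difference 6.8 − 3.7 = 3.1 kg; SD 3.1 kg, read as the SD of individual weight change because it stands beside a difference in weight losses. Standardised effect d = 3.1/3.1 = 1.0.
- Power 80%, alpha 0.05. Sidedness is not stated; two-sided is taken first, then one-sided.
- Stated requirement 10; 14 per group after the dropout allowance.
- Completers per group: 24/2 = 12 from the forecast in Human Participants, item 2, or 14 × 0.8 = 11.2, about 11, from the stated 20% dropout.

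**Reproducing the stated 10**

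One-sample or paired t-test: noncentrality d√n, df = n − 1. With d = 1.0, two-sided 0.05 and 80% power, n = 9.94, so 10. Power is 74.8% at n = 9 and 80.3% at n = 10, an exact match.

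The pre/post calculations in the same item fit the same formula: d = 2/1.2 gives 5.05 and d = 2.4/1.5 gives 5.28, against the stated 5 and 6.

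**The calculation for two independent groups**

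With one measurement before and one after, the group-by-test interaction in two arms is equivalent to a two-sample t-test on the changes: noncentrality d√(n/2), df = 2n − 2, n per group.

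- Normal approximation: n = 2(1.960 + 0.842)²/1.0² = 15.7, so 16 per group.
- t-test: n = 16.7, so 17 per group (power 80.7%). With 20% dropout, 17/0.8 = 21.25, so 22 per group, or 44 against the planned 28.

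Power at the planned sizes, d = 1.0:

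| Completers per group | Basis | Two-sided | One-sided |
|---|---|---|---|
| 11 | 14 less 20% | 60.7% | 73.2% |
| 12 | 24 completers forecast | 64.9% | 76.7% |
| 14 | no dropout | 72.1% | 82.4% |

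One-sided, the requirement is 13.1, so 14 completers per group. That does not reproduce 10 either.

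**Detectable difference.** With 12 per group, two-sided 0.05, 80% power is reached at d = 1.197, that is 1.197 × 3.1 = 3.7 kg. For 10 per group to be enough at a difference of 3.1 kg, the SD would have to be about 2.3 kg; the protocol gives 3.1 kg.

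**Dropout step.** 10/0.8 = 12.5, so 13, not 14. The forecast of 24 from 28 is a loss of 4/28 = 14%, not 20%. Neither changes the conclusion.

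**The contrast**

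| | Arm A | Arm B | What differs |
|---|---|---|---|
| Source of the 3.1 kg | Exercise | Exercise + diet | Diet |
| This trial | Diet | Diet + exercise | Exercise |

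The protocol gives no effect size for the second row.

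**The case against.** **Matched pairs.** The Brief Summary describes match pairing for the exercise-plus-diet and diet groups as well, and Statistical Considerations, item 1, answers that subjects are match paired rather than randomised. On that reading a paired formula is not wrong in itself, and 10 would mean 10 pairs. It would, however, need 3.1 kg to be the SD of the within-pair difference. If 3.1 kg is the individual SD, that requires a within-pair correlation of 0.5; at assumed correlations of 0.25 and 0 the requirement is 14 and 18 pairs. No within-pair SD or correlation is given and no within-pair analysis is planned. The design item, Phase 4 and the non-bariatric schedule all say randomised. The conflict is real, but it does not rescue the 10.

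**Sidedness.** The hypothesis is directional and no sidedness is stated, so the shortfall depends partly on this. One-sided, 12 per group comes close at 77%, and 80% is reached only if almost all 14 per group complete. What remains is that no two-sample reading yields 10.

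**Preliminary study.** Item 3 says that the data will serve as preliminary work for later power calculations. That lowers the weight of the point, but the item goes on to claim 80% power, and a stated figure should be right.

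**Stronger readings the documents do not support.**

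- A reader might infer that true power is 56%, the two-sample value at 10 per group. The protocol does not plan to analyse 10 per group; it treats 14 and expects 12 to complete.
- A reader might infer that weight is the wrong outcome, since the design statement says "insulin sensitivity will be measured before and after interventions across 4 experimental conditions". Weight change is itself listed among the outcomes for the primary objective, so sizing on it is permissible, and moving to the insulin sensitivity index is a preference.
- A reader might argue that 3.1 kg is implausible as an exercise effect over two weeks. That needs an energy value per kilogram which the protocol does not give, and the session count is unsettled: 12 in the description of the exercise arm, visits 4–17 (14 visits) in the schedule.
- A reader might expect a null result to be taken as proof of no exercise benefit. Nothing in the protocol plans that inference.

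**Conclusion.** The point holds. The stated 10 is a two-sided one-sample or paired result applied to two randomised groups. On the protocol's own difference and SD, a two-sided two-sample test needs 17 completers per group, and the planned 11 to 12 give about 61–65% power for a 1-SD difference, or 72% with no dropout. The assumed 3.1 kg is the effect of adding diet, not the effect of adding exercise that Ex+CR versus CR estimates.

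This rests on three assumptions: 3.1 kg is the SD of individual weight change, the non-bariatric arms are independent, and the test is two-sided. Relaxing the last raises power at 12 per group to 77%, still below 80%.

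The paragraph should be corrected. Because the study is described as preliminary and the remedy is wording, this is a should-fix matter and not one that calls the conduct of the trial into question.

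**What to change.** Rewrite the non-bariatric paragraph of Statistical Considerations, item 3, as follows.

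- Give a two-sample calculation for Ex+CR versus CR and state the sidedness of alpha.
- If two-sided, say that 14 treated and 11 to 12 completing per group give about 61–65% power for a difference of 1 SD. Alternatively, say that 80% power is reached only for differences of about 1.2 SD, roughly 3.7 kg at SD 3.1 kg with 12 per group.
- Stop presenting the exercise versus exercise-plus-diet difference as the expected effect. If no estimate for adding exercise is available, say so and give the detectable difference instead.
- While editing, make the dropout allowance, the 14 per group and the forecast of 24 completers agree.

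The cost is protocol wording only. Enrolment, procedures and the planned analysis stay as they are; the stated power becomes less favourable.

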**Outcome assessments pertaining to the primary objective:**

- 1. Assess the absolute mean difference in the 3-hr postprandial glucose AUC between the 2 different conditions undergoing bariatric surgery and the 2 different groups not undergoing bariatric surgery.
  2. Assess the absolute mean difference in the 3-hr postprandial insulin AUC between the 2 different groups undergoing bariatric surgery and the 2 different groups not undergoing bariatric surgery.
  3. Compare the postprandial insulin sensitivity across conditions (as measured by the insulin sensitivity index- ISI; a calculated value based on the glucose/insulin values obtained from the MMTT or OGTT)
  4. Compare the mean change in body fat between groups.
  5. Compare the mean change in body weight between groups.
  6. Assess the change in cardiorespiratory fitness between groups.
  7. Determine and compare the immunophenotype from blood between groups.
  8. Relate the insulin sensitivity responses to the immunophenotyping from blood via correlations.
  9. Relate the pulse wave velocity responses to the insulin sensitivity and immunophenotyping under each condition by calculating a 3-hour pulse wave velocity AUC.
  10. Relate the augmentation index responses to the insulin sensitivity and immunophenotyping under each condition by calculating a 3-hour pulse wave velocity AUC.

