*Exercise training +* diet + *standard medical care for non-bariatric subjects*: Subject’s assigned to this group will participate in diet program as well as the standard medical care outlined above. For the exercise training, subjects will exercise in Memorial Gymnasium under full supervision by an exercise specialist. The subject will be instructed by an exercise specialist to perform exercise at an exercise intensity that alternates between easy and hard (i.e. interval exercise). They will be instructed to exercise for 60 minutes each session. The first 2 days of training will consist of an introduction to the exercise that includes measures of breath samples to ensure proper exercise intensity and determine how much sugar and fat they are burning for energy. On days 3-7 they will exercise in the select exercise intensity (i.e. interval), and on day 8 they will be given the day off. On days 9-13 they will finish the training program. On day 9 subjects will complete their normal exercise session while the study team collects breath samples to account for caloric expenditure during an exercise bout. This will allow the research team to better understand the caloric deficit of each subject when combining diet with exercise. On day 13, breath samples will be repeated to verify exercise intensity and amount of sugar and fat burned for energy. Heart rate will be measured during all exercise sessions to make sure the intensity is appropriate.

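### The non-bariatric groups are sized on the effect of adding diet to exercise, with a one-sample formula, while the trial tests what 2 weeks of exercise adds to diet

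*Protocol*

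**What the plan says.** Statistical Considerations, item 3, says that "subjects undergoing diet+exercise vs. diet intervention will require more subjects" than the bariatric groups. It takes its planning values from a published diet and exercise study and treats weight loss as the measure of energy deficit: "A delta of 3.1kg (Exercise = 3.7kg vs. Exercise+diet = 6.8kg), SD of 3.1kg with 80% power". At an alpha of 0.05 this is said to give 10 subjects, and "assuming a 20% dropout rate, 14 will be required per group".

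Phase 4 (Interventions) says that subjects not having surgery will be "randomized to the exercise + diet + standard care group or diet + standard care group for 2 weeks". Both arms follow the diet programme of 1000–1400 calories per day. For the exercise arm, "They will be instructed to exercise for 60 minutes each session". Training runs on days 1–2 (introduction), days 3–7 and days 9–13, with day 8 off.

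Human Participants, item 2, expects 28 non-bariatric subjects to be treated and 24 to complete. Among the ten assessments listed for the primary objective, item 5 is "Compare the mean change in body weight between groups"; item 4 is the same for body fat.

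**The concern.** The two source arms both exercise and differ by diet. The two trial arms both diet and differ by exercise. The planning difference therefore belongs to another contrast, and the protocol gives no reason why it should carry over to this one or to a 2-week programme. Nor does it give the length of the source study's interventions.

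This is the only sample-size basis offered for the non-bariatric groups. If the difference is too large and the formula is the wrong one, the stated 80% power does not describe the comparison that will be made. A p-value above 0.05 for weight could then be read as showing that exercise adds nothing to diet, when the groups had little chance of showing a realistic difference at the planned SD.

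**Working it through.** **Inputs from the protocol.** Difference 6.8 − 3.7 = 3.1 kg; SD 3.1 kg; power 80%; alpha 0.05 (sidedness not stated, two-sided taken); 24 completers, so 12 per arm if equal; 60-minute sessions; days 1–7 and 9–13, which is 7 + 5 = 12 sessions.

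**Assumptions, not in the protocol.** 5,000–7,700 kcal per kg of weight lost; 300–700 kcal per session; 2-week SD of weight change of 1.0–1.5 kg as an alternative to 3.1 kg.

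**1. Reproducing the stated 10.** The standardised effect is d = 3.1/3.1 = 1.0.
- One-sample or paired t-test, two-sided: n = 9.94, rounded up to 10. This matches.
- Two-sample t-test, two-sided: n = 16.7, so 17 per group. The one-sided version gives 13.1, so 14.

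Only the one-sample or paired calculation gives 10, yet the comparison is between two separate groups. Allowing 20% dropout, 17/0.8 = 21.25, so 22 per group would be enrolled, against the stated 14.

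**2. Power at the protocol's own difference.** Two-sample t-test, d = 1.0, 12 per arm: 65%. At 11 per arm, which is what 20% dropout from 14 implies (14 × 0.8 = 11.2), it is 61%.

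**3. What 3.1 kg would require of the sessions.** The diet is common to both arms, so the planned gap has to come from exercise.
- At 7,700 kcal/kg: 3.1 × 7,700 = 23,870 kcal; divided by 12 sessions, about 1,990 kcal each.
- At 5,000 kcal/kg: 3.1 × 5,000 = 15,500 kcal; divided by 12 sessions, about 1,290 kcal each.
- Counting 14 sessions instead (training visits 4–17 in the non-bariatric schedule): about 1,705 and 1,107 kcal each.

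**4. What the sessions would plausibly add.** Difference = sessions × kcal per session / kcal per kg.
- Low: 12 × 300/7,700 = 0.47 kg.
- At 700 kcal and 7,700 kcal/kg: 12 × 700/7,700 = 1.09 kg.
- High: 12 × 700/5,000 = 1.68 kg.

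The range is about 0.5–1.7 kg, or 15–54% of 3.1 kg. With 14 sessions the high end is 14 × 700/5,000 = 1.96 kg. Even 1,000 kcal per session at 5,000 kcal/kg gives 2.4 kg with 12 sessions and 2.8 kg with 14.

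**5. Power at those differences.** Two-sample t-test, 12 per arm, two-sided 0.05:

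| Difference | SD 3.1 kg (stated) | SD 1.5 kg (assumed) | SD 1.0 kg (assumed) |
|---|---|---|---|
| 0.47 kg | 6.5% | 11% | 20% |
| 1.09 kg | 13% | 40% | 72% |
| 1.68 kg | 25% | 75% | 98% |

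**6. Detectable difference.** With 12 per arm, 80% power needs d = 1.197. At the stated SD that is 1.197 × 3.1 = 3.7 kg, which exceeds the planned 3.1 kg.

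**The case against.** The protocol describes the data as preliminary work for later power analyses, so an imperfect calculation matters less than it would in a confirmatory trial. The stated hypothesis for this pair of arms concerns insulin sensitivity and immune cell dysfunction, and weight is one of ten listed outcomes. The energy figures and the 2-week SD are assumptions, and with a small SD and a difference at the top of the range power reaches 98%. All of this stands. It means that low power for weight is shown at the stated SD and not in general. It does not rescue 3.1 kg as a planning value or the one-sample formula, and the protocol does claim 80% power.

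Three stronger readings are tempting, and the protocol does not support them.

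- A reader might infer that the planned contrast will not arise at all. It will: the exercise is fully supervised, heart rate is measured at every session, and a smaller weight gap is still to be expected.
- A reader might infer that a null result could not be interpreted. A confidence interval remains readable, breath samples on days 9 and 13 document the exercise expenditure, and nothing here shows that the glucose, insulin or immune comparisons fail.
- A reader might take the figure of up to 8 exercise sessions in Biomedical Research, item 2, as a competing number for this cohort. That paragraph speaks of each subject generally, and 8 matches the bariatric schedule (visits 4–11). It is ambiguous, but it is no basis for calculating a non-bariatric exercise dose.

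**Conclusion.** The point holds as a planning error for the non-bariatric cohort. Two faults can be read from the protocol without outside figures: the 3.1 kg comes from the wrong contrast, and the 10 is a one-sample or paired number where two groups need 17 each. The second alone lowers power from the stated 80% to 65% with 12 completers per arm.

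That 3.1 kg is out of reach in 2 weeks rests on assumed energy figures, but no point in the stated range reaches it. At the protocol's SD, power for 0.5–1.7 kg is about 7–25%; at an assumed SD of 1.0–1.5 kg it is 11–98%. A non-significant weight difference would thus be weak evidence of no added effect at the planned SD. Body fat has no planning value of its own, so the same caution applies there.

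**What to change.** In Statistical Considerations, item 3:

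- Withdraw the 3.1 kg and 80% power statement for the non-bariatric groups.
- Keep the planned enrolment. Using a two-sample formula, state the detectable difference or power for diet+exercise versus diet at 2 weeks. With 12 per arm and SD 3.1 kg, the detectable difference at 80% power is about 3.7 kg.
- Base the restated figure on a difference and SD for this contrast and duration, fixed before the data are seen, and show the assumptions as a range.
- State that between-arm differences in weight and fat will be reported with confidence intervals, and that a non-significant result will not be read as no added effect.

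Elsewhere, reconcile the number of non-bariatric training sessions between Phase 4 (12 by its day count) and the non-bariatric schedule (visits 4–17, which is 14), and say which cohort the figure of up to 8 in Biomedical Research, item 2, refers to.

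The cost is protocol text only, with no added subjects or visits and no change to the interventions. The downside is a less favourable stated figure for weight.
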